## Abstract

**Background:**

It has been estimated that approximately 20% of all Swedish children grow up with parents having alcohol problems, which may result in negative outcomes among these children. Therefore, most Swedish municipalities provide resources for support, but at the same time figures reveal that not even 2% receive support, mainly due to difficulties in identifying and recruiting these children into support programs. Delivering intervention programs to children and adolescents *via *the Internet seems a promising strategy, but to date, the number of web-based interventions aimed at this target group is very scarce. We have therefore developed a novel internet-delivered therapist assisted self-management intervention called the web-ICAIP (Individual Coping and Alcohol Intervention Program) for adolescents having parents with alcohol problems. The purpose of the program is to strengthen adolescents' coping behavior, improve their mental health, and postponing the onset or decreasing risky alcohol consumption. This paper describes the web-ICAIP and the design of a randomized controlled trial (RCT) to measure the efficacy of this intervention.

**Methods/Design:**

The RCT will include at least 183 adolescents (15-19 year old) who will be randomly allocated to two conditions where one group has access to the web-ICAIP and the other is a waiting list control group. Participants will be recruited from websites containing information and facts for adolescents about alcohol and other drugs. Possible participants will be screened using the short version of the Children of Alcoholics Screening Test (CAST-6). The assessment consists of a baseline and two follow-up measurements taking place after two and six months, respectively. The primary outcomes include the Center for Epidemiological Studies Depression Scale (CES-DC), a coping behavior scale, and also the short version of the Alcohol Use Disorders Identification Test (AUDIT-C). Additional outcomes include the "Ladder of life" which measures overall life satisfaction and questions concerning program adherence.

**Discussion:**

There is an urgent need for developing and evaluating web-based intervention programs which target children having parents with alcohol problems. This study will therefore make an important contribution to this novel field of research.

**Trial registration:**

ISRCTN41545712

## Background

There are different estimates reported on the prevalence of children having parents with alcohol problems, and these figures all indicate that the problem is wide-spread. For instance, in the U.S. it has been estimated that 28.6% of all children below the age of 18 years are exposed to alcohol abuse or dependence within the family [1], while in 15 European Union countries (and Norway) it has been estimated that between 6.8 and 11.7% of all children below 15 years of age are affected by parental alcohol misuse [2]. In Sweden, it has been estimated that approximately 20% of all children grow up in families where at least one parent has risky alcohol consumption [3].

Children affected by parental substance abuse are at increased risk for many psychological problems (reviewed in [4-6]). For instance, they have an elevated risk of developing internalizing symptoms such as depression and anxiety disorders, and externalizing symptoms such as conduct disorders [6,7]. Additionally, it has been demonstrated that these children may experience poor intellectual, cognitive, and academic achievement [8,9], domestic physical abuse [10], and are at risk of earlier drinking onset [11] and developing substance abuse problems themselves [12-14]. Children growing up in families with substance abuse problems therefore comprise a target group for selective intervention and prevention (reviewed in [15,16]).

In Sweden, the municipalities alone account for the vast majority of support offered to these children. In an annual survey from the junior association of the Swedish IOGT-NTO it is reported that about eight out of ten municipalities provide resources for support [17]. However, estimates also reveal that not even 2% of all these children receive support. Thus, there is an overwhelming majority who never receive support, mainly due to difficulties in identifying and attracting them into intervention programs [15,18].

One appealing strategy to reach out and support a larger number of people is to deliver intervention programs *via *the Internet (reviewed in [19-21]). These web-based interventions seem particularly appealing for adolescents as they generally have good computer skills and often use social media online. Furthermore, research reveal that adolescents regard the Internet as attractive since it is readily accessible and an anonymous means of seeking help [22]. The positive effects of web-based interventions have been demonstrated across a broad range of different conditions and in a comprehensive review by Barak and co-workers, covering 92 studies involving 9764 participants, an overall medium mean effects size was found, which is in line with traditional "face-to-face" therapy [23]. To date, most of these interventions have been designed for adults. However, a few interventions have been reported that target children or adolescents [24,25], but the number of web-based interventions aimed at children of substance abusing parents are still very scarce [15,26].

This paper reports on the design of a novel therapist assisted web-based self-management intervention which has its origin in a manual-based "face-to-face" intervention called the ICAIP (Individual Coping and Alcohol Intervention Program) [27,28] developed at the unit of Clinical Alcohol Research (presently named the Clinical Health Promotion Centre) at the Department of Health Sciences, Lund University and Skåne University Hospital. Previous research on both the ICAIP, aimed at college students who have parents with alcohol problems, and a coping skills intervention program, aimed at spouses of alcoholics, have shown positive effects with regard to decreased alcohol consumption, and improved mental health as well as coping behavior [27-30]. Our hypothesis is therefore that a web-based version of the ICAIP, web-ICAIP, will render in positive effects among a younger target group of 15-19 year olds who have parents with alcohol problems.

### Objective and research questions

The main objective of this study is to evaluate the efficacy of web-ICAIP which is targeted at adolescents aged between 15 and 19 years, having at least one parent with alcohol problems. Specific research questions concerns the participants' improvement in (i) coping behavior, (ii) mental health, and also relates to (iii) alcohol in the sense of postponing the onset or decreasing risky consumption.

## Methods/Design

This study consists of a RCT with two parallel conditions (Figure 1) where one group has access to the web-ICAIP intervention and the other consists of a waiting list control group representing treatment as usual (TAU). The intervention is provided *via *the web portal Drugsmart (http://www.drugsmart.com) which, in addition to more general information about alcohol and other drugs, contains information, facts, and activities targeted to children of substance abusing parents. This information has been available at Drugsmart since 2009 and both the intervention group and the control group will have access to this web site.

**Figure 1 F1:**
[figure not shown]
**Flow chart representing the web-ICAIP study design**.

### The target sample

The sample is to consist of at least 183 adolescents aged between 15 and 19 years. Additional inclusion criteria involve having at least one parent with alcohol problems, easy access to a computer and the Internet, and being sufficiently fluent in Swedish. Participants will be excluded from the study, and referred to appropriate care, if there are indications of either suicidal or self inflicted harm behavior.

### Screening and recruitment

Participants will be recruited through the Drugsmart website and other similar websites by inviting visitors who are 15-19 years old to take part in a web-based survey. Those who agree to participate will access the survey *via *the online survey data collection tool Easyresearch (QuestBack, Norway). Apart from questions concerning age and gender, the participants will be screened for having parents with alcohol problems using the short version of the Children of Alcoholics Screening Test (CAST-6) developed from a 30-item original version [31]. The CAST-6 is a 6-item true/false measure designed to assess whether or not participants perceive their parents' alcohol consumption as problematic, and has proven to be a useful brief screen which compares well to other measures [31,32]. The CAST-6 instrument demonstrates a high internal consistency (r = 0.92-0.94) and test-retest reliability (r = 0.94), as well as a high validity as compared to the 30-item version (r = 0.93) using the recommended threshold score of 3 or higher [31,32]. We have previously translated the CAST-6 into Swedish, and modified it to also include step parents' alcohol consumption, to be used in a feasibility study attempting to measure the prevalence of the problem ([name] & [name] unpublished data).

Those who are eligible to be included in the RCT receive additional information and are asked to participate. It is required that informed consent is given and an e-mail address is provided, which is the only personal identification record collected and our way to communicate with the participants.

### Assessment

A baseline assessment will take place before randomization, and two follow-ups will take place two and six months after the initial assessment. Participants will be invited to each assessment by e-mails and if necessary, up to three reminders will be sent 5, 10, and 15 days after the first invitation. All assessments are online surveys distributed as described above. To enhance response rates, participants will receive an e-mail containing a cinema gift certificate corresponding to 11 Euros as compensation for completing each assessment. If a participant completes all assessments an additional gift certificate will be given. The participant can subsequently receive four cinema gift certificates totaling 44 Euros.

### Outcome measurements

#### Primary outcomes

To measure depressive symptoms, the child version of the Center for Epidemiological Studies Depression Scale (CES-DC) will be used [33]. This scale measures depressive symptoms during the past week using four-point likert scales, where a higher total score indicate more depressive symptoms. Additionally, this scale has been shown to be a rather general measure of childhood psychopathology [34], and has been demonstrated to be reliable and valid among Swedish adolescents [35].

A coping behavior scale for children of alcoholics has previously been developed at the unit of Clinical Alcohol Research. This scale is based on the Coping Behavior Scale by Orford and co-workers [36] and has been demonstrated to be reliable [27,28]. For the purpose of this study, this scale has been factor analyzed to reduce the number of questions from 37 to 20. The scale measures four coping typologies (discord/emotion, control, relationship, and avoidance) using four-point likert scales, and a threshold score above 50 points (out of 80) indicate a dysfunctional coping behavior.

Alcohol consumption will be assessed using the short version of the Alcohol Use Disorders Identification Test (AUDIT-C) [37], assessing frequency of drinking, the quantity consumed at a typical occasion, and the frequency of heavy episodic drinking. These questions have previously been translated into Swedish [38]. Furthermore, two additional questions will be added concerning whether or not the respondents have ever consumed alcohol to the point that he/she felt intoxicated, and respondents' age of onset of drinking and intoxication.

#### Additional outcomes

Overall life satisfaction will be measured by asking about the participants' past, present, and future rating of his/her life on a ten-point "Ladder of life" representing life status from "worst" to "best" possible life imaginable [39]. The original version was designed for adults and asked the respondents to reflect over the past, present, and future in a five-year perspective. A modified version for children, using a shorter time-frame of one year, has been used previously in Sweden [40] and will be used in this study.

In addition, information about demographics and any previous or present participation in support groups for children of alcoholics will be assessed. Finally, program adherence will be measured in terms of completed film-based lectures and exercises (see below), and respondents' activity at the Drugsmart website will be assessed.

### Randomization

After completing the baseline assessment, each participant will be allocated to the intervention or the control group. An unrestricted random allocation sequence will be generated by an external researcher using the Random Allocation Software [41]. Participants will be informed about their allocation by e-mail, and those who are randomized to the treatment group receive a username and password in order to be able to login to the web-ICAIP website. All participants are informed that they have access to all the other content on the Drugsmart website.

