### Sample size

This trial is designed to detect a medium or larger effect size, corresponding to a standardized mean difference (Cohen's d) of > 0.5 [43]. An *a priori *calculation of the estimated sample size, using the software G*Power [44] reveals that it is required that a total of 128 participants (64 in each group) enroll in the trial (power = 0.80, α = 0.05, 2-tailed). However, in a pilot study of a web-based intervention aimed at young people having at least one parent diagnosed with a psychiatric or multiple psychological disorders, or an addiction problem, the attrition rate was found to be 28% [26]. Assuming a similar attrition rate of 30%, we therefore need to enroll a minimum of 128/(1-0.3) = 183 participants in the trial.

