### Strengths and limitations

The present study has a number of strengths. First, the web-ICAIP is a web-based intervention program, and it appears as if the Internet is a particularly promising way to provide support to adolescents growing up with parents having alcohol problems, since it offers an anonymous means of communicating and makes intervention programs readily accessible [22]. Additionally, this program is one of the first web-based interventions aimed at this target group and may prove to be an effective strategy to deliver, not only therapist assisted self-management programs, but also other forms of support such as online support groups. Another strength is that the web-ICAIP involves personalized tailored feedback, in the form of pre-written automatic messages and therapist-written personalized feedback, both of which has proven to be important components in web-based interventions aimed at adolescents [45]. Finally, this study attempts to evaluate the efficacy of web-ICAIP using a RCT study design, which is considered to be the strongest experimental design with regards to allocation bias, thus increasing the probability that participant characteristics in the two conditions are similar.

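### Baseline drinking status is neither balanced by the unrestricted allocation nor used in the analysis as described, which gives up some precision on AUDIT-C

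*Protocol article*

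**What the plan says.** Three parts of the protocol article bear on this point.

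- **Randomization.** Allocation follows completion of the baseline assessment, and "An unrestricted random allocation sequence will be generated by an external researcher using the Random Allocation Software". No blocks or strata are named.
- **Sample size.** The target effect is given as "corresponding to a standardized mean difference (Cohen's d) of > 0.5". With "power = 0.80, α = 0.05, 2-tailed" the article finds that "it is required that a total of 128 participants (64 in each group) enroll in the trial", and after an allowance for 30% attrition, "we therefore need to enroll a minimum of 128/(1-0.3) = 183 participants in the trial".
- **Analyses.** Outcomes at baseline and follow-up are compared within and between groups, with multiple imputation and Cohen's d as the effect measure. No covariate is mentioned.

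Gender is asked at screening. The questions on drinking, including whether the respondent has ever been intoxicated, are listed under Primary outcomes, and the baseline assessment precedes randomisation. Both facts are therefore known before a participant is allocated. Under Strengths and limitations, the randomised design is credited with "increasing the probability that participant characteristics in the two conditions are similar".

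**The concern.** The third research question concerns delaying the start of drinking or reducing risky drinking. Someone who already drinks cannot delay the start, and someone who does not drink cannot cut down. What the AUDIT-C comparison can show therefore depends on the mix of drinkers and non-drinkers in each arm. The intervention also reflects this difference, since two optional lectures are meant for participants with risky consumption.

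Baseline drinking is thus an obvious prognostic factor for AUDIT-C, and the plan as described does nothing with it. Unrestricted allocation leaves its balance to chance, and an unadjusted comparison leaves its contribution in the error term. The stake is a less precise estimate on one of three primary outcomes, and a result that is harder to read if the arms happen to differ in drinking at baseline.

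**Working it through.** **1. The plan's own figures.** A two-sample t test with d = 0.5, two-sided alpha 0.05 and power 0.80 needs 63.77, rounded up to 64 per group; power at 64 per group is 0.801. Attrition: 128/(1 − 0.3) = 182.86, rounded up to 183. Both figures reproduce.

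**2. What unrestricted allocation does to arm sizes.** One arm's size is Binomial(183, 0.5), with SD √(183 × 0.25) = 6.8 and 95% range 78 to 105. Power after 30% attrition is 0.802 at 91/92 and 0.793 at 78/105. The effect on power is under 1 point.

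**3. What it does to baseline balance.** For a factor with prevalence p, the difference in its share between arms has SD √(p(1 − p) × 2/91.5). The article gives no prevalence, so a range is shown.

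| Assumed p | 95% range of the difference, 183 randomised | Chance of a gap over 10 points |
|---|---|---|
| 50% | ±14.5 points | 18% |
| 70% | ±13.3 points | 14% |
| 80% | ±11.6 points | 9% |
| 90% | ±8.7 points | 2% |

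**4. Is this imbalance an additional error?** No. The standard error of the mean difference with 183 is about 2/√183 = 0.148 SD. A factor with p = 50% that shifts the outcome by 1 SD contributes 0.074 SD through chance imbalance, and (0.074/0.148)² = 25% of the variance. That share is already inside the total SD on which Cohen's d is defined. It is error that adjustment can remove, not error that the sample size overlooked.

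**5. What adjustment gains.** Let s be the shift in AUDIT-C, in SDs, between those with and without the factor (assumed 0.5 to 1). The factor explains R² = p(1 − p)s² of the variance, and adjustment raises the effective effect size to 0.5/√(1 − R²). The formula column uses 64 per group. The simulated columns use 128 analysed, a continuous outcome and a linear model, with 100,000 trials per setting for unrestricted allocation and 20,000 for stratified blocks of 4.

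| p, s | R² | Effective d | Power, formula | Simulated: unrestricted, unadjusted | Simulated: unrestricted, adjusted | Simulated: stratified and adjusted |
|---|---|---|---|---|---|---|
| 50%, 0.5 | 0.0625 | 0.516 | 0.826 | 0.797 | 0.818 | 0.824 |
| 50%, 1 | 0.25 | 0.577 | 0.900 | 0.799 | 0.894 | 0.897 |
| 80%, 0.5 | 0.04 | 0.510 | 0.817 | 0.799 | 0.811 | 0.816 |
| 80%, 1 | 0.16 | 0.546 | 0.865 | 0.799 | 0.861 | 0.863 |

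Adjustment lifts power from about 0.80 to between 0.81 and 0.90. Stratifying on top of it adds 0.2 to 0.5 points, close to the simulation error of about 0.2 to 0.3 points. Stratifying without adjusting gives 0.805, 0.830, 0.804 and 0.821, so it recovers only part of the gain. With no true effect, the unadjusted test under unrestricted allocation rejects in 5.0% to 5.1% of trials, as it should.

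**The case against.** The strongest reply is that nothing here is an error. Unrestricted allocation is a valid method, chance imbalance does not bias the comparison or inflate the type I error, and the article promises no exact balance. Its remark on similar characteristics claims only a higher probability, which is true of simple randomisation. Covariates are also commonly named in a statistical analysis plan, and none is shown. All of this stands, and it is why the point is limited to precision and offered as an improvement. What remains is that the article does fix the allocation method, which no later analysis plan can change once participants are randomised, and that the analysis as described leaves a relevant, already collected variable unused.

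A reader might infer more, and the document does not support it:

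- **That 183 is wrong because it is odd, and should be 184.** The article gives 183 as a minimum, and a 91/92 split has power 0.802.
- **That the plan's 64 per group is put at risk by unequal allocation.** That figure is the number wanted after attrition, not the split at randomisation. With independent 70% retention, both arms keep at least 64 in 19% of trials under unrestricted allocation and in only 31% at 91/92. Blocks would not secure it, and power barely depends on it.
- **That imbalance could move the result by up to 0.145 SD, or 29% of the target effect.** That takes an assumed prevalence of 50% and an assumed shift of 1 SD at the 95% extreme, and counts again what is already in the sampling error (step 4).

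**Conclusion.** The point holds as a minor improvement. Baseline drinking status is directly relevant to AUDIT-C and to the third research question, is known before allocation, and is neither balanced nor adjusted for in the plan as described. The sample size and the stated power stand, and the comparison is unbiased. Under the assumed prevalences and shifts, the precision given up corresponds to roughly 1 to 10 points of power on AUDIT-C, nearly all of it recoverable by adjustment alone. The size rests on those two assumptions and on treating AUDIT-C as a continuous score in a linear model. Nothing was calculated for CES-DC or the coping scale. The article does not say how strongly sex predicts AUDIT-C, so no separate gain is claimed for it.

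**What to change.** **Main change.** In Analyses, state that the between-group comparisons will include baseline drinking status (ever having been intoxicated, yes or no) and sex as covariates. Standardise Cohen's d by the unadjusted SD, so that it keeps its meaning against the 0.5 in the sample size. No new data are needed and the sample size does not change. The cost is a sentence and two model terms, fixed before outcome data are seen.

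**Optional change.** In Randomization, have the external researcher generate the sequence in permuted blocks of randomly varying size, stratified by ever having been intoxicated and, if wished, by sex. This makes four lists instead of one. The downside is that the stratum must be read from the baseline survey before each allocation. The extra power beyond adjustment is under 1 point in the settings checked, so the main reason to do it would be visible balance at baseline. If it is adopted, keep the stratification factors in the model.

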### The intervention

The web-ICAIP is derived from the manual-based face-to-face ICAIP intervention program [27,28]. The ICAIP consists of a combination of an alcohol intervention program, which follows the short version of the Brief Alcohol Screening and Intervention for College Students program (BASICS) [42] and a coping intervention program, and was elaborated in the research group of Clinical Alcohol Research. The program was evaluated in a RCT on adult children of alcoholics who were studying at university level during 2000-2001 [27,28].

Similar to the original ICAIP intervention, the web-ICAIP is divided into an alcohol and a coping theme, consisting of film-based lectures and stories, various exercises, and personalized feedback. Briefly, once the participants have logged into the website they are introduced to the program followed by three film-based lectures (between 8 and 15 minutes each) concerning alcohol problems within the family. There are two additional film-based lectures about alcohol which is optional and aimed at participants with risky alcohol consumption. After completing the lectures, the participants have to go through some exercises concerning alcohol and coping, and thereafter receive a pre-written automatic feedback message. This is followed by some brief information about coping patterns in families of alcoholics as well as emotion- and problem-focused coping. The participants then have to go through and read four so called "readers' letters" which relates to coping and alcohol problems in the family and are presented by film-based introductions each being a few minutes long. Based on these stories, the participants are requested to complete a coping-focused exercise and finally, to reflect over their own family situation.

After a few days, the participants receive an automatic personalized feedback. This feedback compose a library covering all pre-written feedback messages, each one being tailored towards the participants' specific responses during the exercises. The feedback also includes suggestions from experts (*i.e*., therapists who were involved in the development of the intervention) on how to cope and act in the future. In the last part of the intervention the participants also formulate their own action plan for the future. The participants can enter and exit the web-ICAIP anytime during the study period but only receives the personalized feedback once. Since it is recommended that a few days pass in between the different lectures etc., the total estimated time for completing the program is between one and two weeks.

